**Table 2. Estimated cumulative incidence of HPV16/18 persistent infections according to the participant's age**

| Follow up (years) | Age (years) | Cumulative incidence of HPV16/18 persistent infections (%) |
|-------------------|-------------|------------------------------------------------------------|
| 0                 | 15          | 0,09                                                       |
| 1                 | 16          | 1,48                                                       |
| 2                 | 17          | 3,41                                                       |
| 3                 | 18          | 6,10                                                       |
| 4                 | 19          | 9,83                                                       |
| 5          | 20   | 15,02                                                      |
| 5,5        | 20,5 | 17,62                                                      |
| 6          | 21   | 20,21                                                      |
| 6,5        | 21,5 | 22,81                                                      |
| 7          | 22   | 25,40                                                      |
| 8                 | 23          | 30,68                                                      |
| 9                 | 24          | 35,95                                                      |
| 10                | 25          | 39,68                                                      |

**Table 3. Sample size needed per group for a statistical power of 90% and number of participants to be recruited depending of the duration of follow up (participant's age), cumulative incidence of persistent infections per age and losses to follow up per year of follow up.**

| Follow-up  | Age         | Cumulative incidence of HPV16/18 persistent infections (%) | Losses to follow-up (%) | Effective sample size (per group) | Number of participants to be recruited (per group) |
|------------|-------------|------------------------------------------------------------|-------------------------|-----------------------------------|----------------------------------------------------|
| 0          | 15          | 0,09                                                       | 0                       |                                   |                                                    |
| 1          | 16          | 1,48                                                       | 1                       |                                   |                                                    |
| 2          | 17          | 3,41                                                       | 2                       |                                   |                                                    |
| 3          | 18          | 6,10                                                       | 3                       |                                   |                                                    |
| 4   | 19   | 9,83                                                | 4                | 2186                       | 2420                                        |
| 5   | 20   | 15,02                                               | 5                | 1431                       | 1667                                        |
| 5,5 | 20,5 | 17,62                                               | 5                | 1220                       | 1496                                        |
| 6   | 21   | 20,21                                               | 5                | 1063                       | 1372                                        |
| 6,5 | 21,5 | 22,81                                               | 5                | 942                        | 1280                                        |
| 7   | 22   | 25,40                                               | 5                | 846                        | 1210                                        |

|    |    |       |   |     |      |
|----|----|-------|---|-----|------|
| 8  | 23 | 30,68 | 5 | 700 | 1054 |
| 9  | 24 | 35,95 | 5 | 598 | 948  |
| 10 | 25 | 39,68 | 5 | 541 | 903  |

### 3.8.2 Sample size for the immunogenicity section

Various options for the calculation of the sample size needed for the immunogenicity section were analyzed. Various laboratory tests (cLia, total IgG, neutralizing antibodies, etc.) were performed during previous studies on the topic, resulting in an important heterogeneity in seropositivity levels and antibody titers reported after 2 or 3 doses of Gardasil®(32,34,35).

Taking into consideration that there is no « gold standard » for the laboratory tests measuring antibodies against HPV and that the sensitivity of the tests currently used varies significantly from one test to another, it was decided not to base the sample size calculation on seropositivity. We have assumed appropriate to base our sample size calculation on the ratio of geometric mean titers (GMT) expected in the 2 study groups (GMT2/GMT3).

The lower limit of the GMT ratio's confidence interval was set at 0.5, given that it is generally the case in this type of study(85,86). Because of potential clinical impacts, and future public health decisions, we want to have enough statistical power to detect a ratio  $\geq 0.65$  between the groups. To demonstrate a ratio of 0.65 between GMT2/GMT3 with a lower limit higher than 0.5, a statistical power of 90% and a significance level of 5%; the sample size needed is a total of 138 participants assessed per group at the end of the study (Table 2).

Taking into consideration a full respect of the study protocol (per-protocol) of 80 to 90% and a loss to follow up of about 5% per year, the enrolment of 500 participants (250 per group) was deemed necessary to be able to establish non-inferiority between the two study groups with a statistical power  $\geq 90\%$  ( $\alpha = 5\%$ ). The enrolment of 500 participants at the beginning of the study (month 60 post primary immunization) will enable us to have at least 138 participants assessed at the end of the study.

Table 2. GMT2/GMT3 ratio: non-inferiority test with a lower limit set at 0.5

| Lower limit | Ratio | N per group |
|-------------|-------|-------------|
| 0.5         | 0.55  | 1034        |
| 0.5         | 0.6   | 284         |
| 0.5         | 0.65  | 138         |
| 0.5         | 0.7   | 84          |

### 3.8.3 Statistical power for the objectives on the impact on condylomas

The very low expected frequency of condylomas in both study groups predicts a low statistical power; this is why these are exploratory objectives. Ecological studies suggest a very high efficacy on the reduction of condylomas(87–89). However, there are no data available to calculate a sample size in order to check if a 2-dose schedule is non-inferior to a 3-dose schedule in the prevention of condylomas. Given that a questionnaire already has to be administered in order to collect

information on confounding factors, adding a question on the diagnosis of condylomas will result in almost no additional costs or inconvenience. On the other hand, we believe that this procedure will bring useful information on HPV vaccine schedules' impact on condylomas in Quebec. An information that is otherwise very difficult to obtain given that there are no reliable diagnostic code(s) to check this issue using administrative databases. Moreover, given that HPV genotyping will enable identification of HPV types 6 and 11, it will be possible to link the presence of these genotypes in vaginal secretions to the clinical diagnosis of condylomas.

#### 3.8.4 Feasibility of enrolment and follow-up.

Every year, about 8,000 girls are vaccinated with 2 doses of HPV vaccine in the two main health regions (Montreal and Capitale-Nationale [Quebec city region]). We plan to increase the radius of enrolment to neighboring towns and towns in the vicinity (using the area covered by the CLSC of residence and postal codes) of the two research centres (e.g. Laval, Montérégie, Chaudières-Appalaches, Saguenay-Lac-Saint-Jean). This will enable an increase of the number girls that could be invited to participate. Enrolment will be done over 4 years. By inviting all the girls in a cohort (e.g. the first cohort will be those vaccinated in 2008-2009) with a 10% participation rate ( $14\,500 \times 0.10 = 1\,450$ ), we will be able to achieve our enrolment objective. According to the assumptions detailed in section 3.8.1, and in order to fulfill our objective, we will have to accrue between 22 and 52 persistent infections. We will have to follow-up each cohort for a minimum of 5 years in order to accrue this number of outcomes.

Many strategies implemented in these studies to maintain the children's participation to the study will be repeated here (e.g. identifying more than one postal address and more than one phone number, sending SMS yearly, etc.). We will equally ask the participants' authorization to obtain their contact information from the Quebec health Insurance Board in case we have difficulties getting in touch with them.

### 3.9 Analysis

Descriptive analyses will be used to describe the participants and compare the two study groups. Specifically, the following analyses will be performed for each of the objectives mentioned in section 2.

For the primary objective:

A survival analysis (time to event analysis) will be performed in order to answer the main study questions. This approach will take into consideration the different duration of follow-up resulting from the fact that the date of entry in the cohort will vary between participants. Time 0 will be defined as the date of randomization. The time of event will be defined as the first occurrence of a persistent infection. Participants with no persistent infection will be censored (right-censored) at: (a) loss to follow-up, (b) death or (c) end of the study whichever comes first. The preliminary analyses will include the comparison of the Kaplan-Meier curves using a non-parametric test (*log-rank test*, *Wilcoxon*) describing how the proportion of participants developing a persistent infection varies over time in each group. The main non-inferiority analysis will rely on the Hazard ratio's (HR) 95% confidence interval. Adjusted analyses will take into consideration the potential confounding factors collected with the annual questionnaire. If the HR's upper limit is not higher than 1.05 (representing a 5% difference of efficacy between the two schedules), we will conclude to a non-inferiority of the 2-dose calendar.

This analysis will then be repeated with the « intention-to-treat » method to evaluate the differences generated by a change in the exposure's definition. Sensitivity analyses will also be performed to evaluate the impact of modifying the outcome's definition. Indeed, it is likely that some girls will not exactly respect the vaginal self-samplings' schedule. We will vary the primary outcome's definition (e.g. consider as persistent infection only if the sample were consecutive and 6 months apart, or

consider as persistent infection a situation where the same type of virus was identified in two consecutive samples regardless of the number of months between the samples).

For the secondary objectives on immunogenicity (objectives 2.2.a and c), two analyses will be performed to measure non-inferiority at month 120:

1) An intention-to-treat analysis (*ITT analysis*) in which all the serologic results available will be included.

2) A per protocol (*according to the protocol, ATP analysis*) which will only include the participants who respected all the procedures planned in the protocol related to the immunogenicity analysis.

All the statistical tests will be performed with a type I error set at 5%. Percentages of seropositivity will be compared with a Chi square or Fisher test. GMTs will be compared with a *t*-test.

Among seropositive samples, GMTs will be calculated for each of the 3 time points planned in the protocol. GMTs obtained in the two groups at different study points will be compared using an analysis of variance (ANOVA) and a Duncan's multiple range test performed with SAS version 9.1.

For the other secondary objective on condylomas (2.2.d), we will mainly perform descriptive analyses as described at the beginning of this section.

An exact poisson regression is planned at the end of the study to compare the persistent infections observed among the vaccinated girls of the two study groups to that of an historical cohort of unvaccinated girls. Therefore, we will be able to calculate the number of persistent infections prevented by vaccination i.e. the difference between the expected and observed number of persistent infections (2.2.e).

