### **3.2 Study population**

We will invite girls who initiated vaccination with Gardasil® in 2008, 2009, 2010 and 2011 at 9-10 years old (see explanation in section 3.4), who received 2 doses at a 6-month interval (minimum of 4 months and maximum of 12 months between doses) and are living in the Montreal, Quebec city (Capitale-Nationale) or Saguenay-Lac-Saint-Jean regions at the time of enrolment to participate to this study (the enrolment areas will be defined using the postal codes closest to the participating research centers). The girls will be invited about 5 years after the beginning of

vaccination, in such a way that during fall 2013 we will start inviting the girls who initiated vaccination in the fall 2008 as part of the school-based vaccination program. In 2014, we will invite the girls who initiated vaccination during fall 2009, in 2016 we will invite those who initiated vaccination during fall 2010, and in 2016 we will invite those who initiated vaccination during fall 2011 (see figure on conduct of the study, appendix B).

The only inclusion criteria are:

- To have received 2 doses of Gardasil® at a 6-month interval (minimum of 4 months and maximum of 12 months between doses) in 4th grade in 2008-2009, 2009-2010, 2010-2011 or 2011-2012;
- To understand French or English;
- To give an informed consent (girl and parent);
- To live in one of the targeted regions;
- To not be pregnant at the time of enrolment;
- To not be considered as immunodeficient at the time of enrolment, and at vaccination in 4th grade.

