### **3.3 Enrolment**

After approval by the Commission d'Accès à l'Information we will contact the Quebec health insurance board (Régie de l'Assurance Maladie du Québec, RAMQ) in order to obtain the contact information of girls aged 9 years on September 30th, 2008 (i.e. born between October 1st, 1998 and September 30th, 1999 for the first enrolment year), 9 years on September 30th, 2009 (i.e. born between October 1st, 1999 and September 30th, 2000 for the second enrolment year), 9 years on September 30th, 2010 (i.e. born between October 1st, 2000 and September 30th, 2001 for the third enrolment year), 9 years on September 30th, 2011 (i.e. born between October 1st, 2001 and September 30th, 2002 for the fourth enrolment year).

From September 2013 to June 2014 we will contact the girls' parents by mail to invite those who received 2 doses of Gardasil® during the 2008-2009 academic year. The letter will explain the purpose of the project, how it will be carried out and details on inclusion criteria. This same step will be carried out in 2014, 2015 and 2016.

A phone number and an e-mail address will enable parents to contact a research nurse (1) to obtain further information, (2) to check eligibility and (3) to take an appointment with a research nurse at the coordinating center.

During this appointment, the research nurse will confirm the participant's eligibility, will obtain informed consent from the girl and her parent, will perform a urine pregnancy test on the girl and will randomize her to one of the groups, administer the 3rd dose if she was assigned to the «3rd dose» group and collect the blood sample if she is part of the subgroup targeted by the secondary objective on immunogenicity. A financial compensation will be offered to the girl and parent 20,00\$ each) for this face-to-face appointment. The participant will collect the first HPV vaginal sample after receiving explanations on the self-sampling procedure and will fill the first questionnaire. A financial compensation will be provided for each self-sampling kit received (5,00\$ per sampling, then 10,00\$ per sampling when the girl turns 18 years of age).

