## **3.5 Study variables and effect measures**

### **3.5.1 Intervention: definition and measurement**

The main variable of interest is the number of Gardasil® doses received. It will be determined experimentally and will only have 2 possible values: 2 doses or 3 doses, the 3rd dose being the one administered by the research nurse during the face-to face-appointment. In order to have non-inferiority estimates as conservative as possible, a «per protocol» approach will be used during analyses as recommended for non-inferiority randomized trials(63). Participants who did not receive the number of doses planned in the protocol will be excluded from this analysis. This number will likely be limited given that the 3rd dose is given immediately after randomization. The experience with the school-based program show that very few girls randomized to the «2 doses» would have already received a 3rd dose (or more) out of the provincial public vaccination program (e.g. paying for an additional dose at a CLSC or a medical clinic during the 4 years following administration of the 2 first doses in 4th grade) ([name]'s personal communication, source: VAXIN database, Capitale-Nationale region). Girls will be regularly questioned on the subject and will be excluded from the per protocol analysis in case they have received an off-protocol dose of Gardasil®, Gardasil® 9 or Cervarix®. However, an intention-to-treat analysis will equally be performed and will include them (see section 3.9 analyses).

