### **3.5.2 Primary outcome: definition and measurement**

The primary outcome will be the cumulative incidence of persistent HPV 16 or HPV 18 infections. The ultimate goal of HPV vaccination is to reduce cervical cancer's incidence and mortality. However, these reductions are only expected in 30, maybe 40 years. It is not desirable to wait that long before evaluating and if necessary adjusting the vaccination program. Therefore persistent infection is the surrogate outcome preferred by many organisations (e.g. WHO) when decisions on efficacy have to be taken in a relatively short time (10 years)(64,65). A persistent infection predicts the risk of precancer very well and is relatively easy to measure and replicate.

A persistent infection will be defined as the presence of HPV 16 or HPV 18 DNA in 2 specimens of vaginal self-samples over 2 consecutive samplings. The samples will be collected every 6 months. Self-sampling is done with a swab inserted in the vagina then stored in an empty vial, before being sent through postal mail. This process has been successfully used by various teams in similarly aged populations(66).

In this definition of persistent infection, we will accept 2 consecutive samples performed at a minimum of 5-month interval and a maximum of 15-month interval. Two-step HPV DNA identification will be performed to minimize the costs. First, a generic test will be performed in order to check if HPV DNA is present. Then a Linear Array test will be performed on positive samples in order to identify the type(s) of HPV. Each type will be counted separately.

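### An HPV 16 or 18 infection already present in the enrolment swab can count as a primary event. The bias is toward HR = 1 but small on the protocol's own figures

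*Protocol*

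**What the plan says.** Five rules, all in the protocol, decide what counts as a primary event.

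- **Time origin and event (3.9).** "Time 0 will be defined as the date of randomization". "The time of event will be defined as the first occurrence of a persistent infection".
- **Persistent infection (3.5.2).** It is the "presence of HPV 16 or HPV 18 DNA in 2 specimens of vaginal self-samples over 2 consecutive samplings". On spacing, "we will accept 2 consecutive samples performed at a minimum of 5-month interval and a maximum of 15-month interval".
- **First swab (3.3).** It belongs to the visit at which the girl is randomized and, if so assigned, vaccinated: "The participant will collect the first HPV vaginal sample after receiving explanations on the self-sampling procedure".
- **Eligibility (3.2).** A closed list, introduced by "The only inclusion criteria are". It covers earlier doses, language, consent, region, pregnancy and immune status. It has no condition on HPV status or sexual experience.
- **Per-protocol set (3.5.1).** "Participants who did not receive the number of doses planned in the protocol will be excluded from this analysis". Off-protocol HPV vaccine doses are also a reason for exclusion. Baseline infection is not.

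The sensitivity analyses that section 3.9 gives as examples vary only the spacing of the two samples.

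**The concern.** An enrolment swab and a month-6 swab are consecutive and lie within the accepted interval, so a positive pair meets the definition. The infection was there when the third dose was given. If that dose does not clear an existing infection (an assumption, usual for a preventive vaccine), the event says nothing about the two schedules.

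Up to randomization both groups had the same two doses, so these events are equal in expectation. Adding the same number to each side pulls the HR toward 1. In a superiority trial that would cost power. Here, if two doses are truly worse, it makes non-inferiority easier to declare. With only 23 persistent infections planned, even a few uninformative events could be a noticeable share.

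**Working it through.** **Plan's own figures.** Section 3.8.1 gives an effective size of 1431 per group, a 5-year cumulative incidence of 15.02%, and efficacies of 95% and 94%.
- Recruitment: 1431 / (0.99 × 0.98 × 0.97 × 0.96 × 0.95) = 1667.3 (stated: 1667).
- Events: 1431 × 0.1502 × (0.05 + 0.06) = 23.6 (stated: 23).

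**Infections present at enrolment.** The only documented input is the cumulative-incidence table in section 3.8.1: 0.09% at follow-up 0 (age 15), a rate before any vaccine efficacy is applied. Section 3.8.1 reports 3364 girls randomized, about 1682 per group.
- At 95% efficacy: 3364 × 0.0009 × 0.05 = 0.15 events in total, 0.076 per group.
- With no efficacy (extreme case): 3364 × 0.0009 = 3.03 events in total, 1.51 per group.

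**Effect on the HR.** For rare events and equal groups, HR ≈ (e2 + b) / (e3 + b), where e2 and e3 are the post-randomization events in the 2-dose and 3-dose groups and b is the baseline events per group. The 3-dose group has e3 = 1431 × 0.1502 × 0.05 = 10.75.

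| True HR | e2 | b = 0.076 | b = 1.51 |
|---|---|---|---|
| 2.0 (efficacy 90% v 95%) | 21.49 | 21.57 / 10.82 = 1.99 | 23.00 / 12.26 = 1.88 |
| 1.2 (94% v 95%) | 12.90 | 12.97 / 10.82 = 1.20 | 14.41 / 12.26 = 1.18 |
| 1.05 (limit in 3.9) | 11.28 | 11.36 / 10.82 = 1.05 | 12.79 / 12.26 = 1.04 |

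At a true HR of 2.0 the base is 21.49 + 10.75 = 32.2 events. The 23 events belong to the 1.2 scenario.

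**Effect on one-sided type I error.** The normal approximation is Φ(ln(margin / h) × √D / 2 − 1.96), where h is the diluted HR and D the total events. Without baseline events it is 2.5%.
- Margin 2.0 (95% to 90% efficacy, section 3.8.1), 32 post-randomization events: about 2.6% for b = 0.076. For b = 1.5, h = 1.88 and D = 35, and the result is 3.8%.
- Margin 1.05 (section 3.9), 23 post-randomization events: 2.6% even for b = 1.5. At that margin 23 events would need an observed HR of about 1.05 × exp(−1.96 × 2 / √23) = 0.46 to pass, so the dilution is immaterial.

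**Plausibility check.** All persistent infections expected by year 1, new ones included, are 1682 × 0.0148 × (0.05 + 0.06) = 2.7 at 95% and 94% efficacy. At 95% and 90% they are 1682 × 0.0148 × 0.15 = 3.7. Three baseline events is therefore already an extreme figure.

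**The case against.** The strongest reply is that this is a clarification. The protocol calls its outcome a cumulative incidence and speaks of prevention and of participants developing an infection, all of which point to new infections. How girls already infected at entry are handled is often written in a statistical analysis plan, which is not shown. On the documented input the HR does not move visibly, and under the written limit of 1.05 the decision would not change.

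The point about size stands in full. The point about the analysis plan stands only in part: the protocol itself fixes the time origin, the event, eligibility and the per-protocol exclusions, and together these admit the baseline infection. The word incidence signals an intention that no rule enforces.

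Two stronger readings are tempting.
- A reader might infer a material bias. If 0.3% of girls were positive at baseline and half of those infections persisted, 3364 × 0.003 × 0.5 = 5 events would be added, and an HR of 2.0 would read (21.5 + 2.5) / (10.7 + 2.5) = 1.82. The documents support neither input, and 5 events exceed the 2.7 to 3.7 expected in the whole first year.
- A reader might also see a contradiction with the wish in section 3.5.1 for conservative estimates. That sentence concerns doses received, not infection at entry, so there is none.

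**Conclusion.** The gap is real. As written, an HPV 16 or 18 infection found in the enrolment swab and again at the next sample is a primary event, and nothing in eligibility or the per-protocol rules removes it. The direction is anti-conservative when two doses are truly worse.

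The expected size is small: about 0.15 events, rising to about 3 only if two doses gave no protection at all. The result rests on three assumptions: the 0.09% stands in for infection present at enrolment, pre-existing infections are balanced by randomization, and the third dose does not clear them. The 0.09% counts persistent infections. Single-sample DNA positivity at baseline is not given and could be higher.

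The implied margin of 2.0 in section 3.8.1 and the limit of 1.05 in section 3.9 do not agree. That is a separate matter, and the effect is shown for both. The case for acting is a clear logical gap and a nearly free remedy, not a large expected bias. Priority is low.

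**What to change.** In sections 3.5.2 and 3.9, state that in the per-protocol primary analysis an event for HPV 16 or HPV 18 counts only in girls whose enrolment-visit swab was negative for that same type. Treat that swab as baseline whether it was taken just before or just after randomization. Say how a missing or inadequate enrolment swab is handled. Keep all events in the intention-to-treat analysis, so that the effect of the rule can be seen.

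Requiring both positive samples to be dated after randomization would not be enough. Section 3.3 describes the swab after randomization and the dose, so it may fall after randomization on the same day. In addition, a girl positive at enrolment, month 6 and month 12 would still qualify through the later pair.

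The cost is wording and programming, as the swabs are already collected, and possibly a few fewer events. Because baseline status is sampled at the visit of the dose, the schedule can hardly influence it, so a type-specific exclusion should keep the randomized comparison intact. The same rule should be applied, or its absence noted, in the comparison with unvaccinated cohorts (sections 3.5.3 e and 3.9) and in the definitions harmonized with QUEST (section 1.6).
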